### Data collection tools

#### Self-administered questionnaire – year 1, 2, and 3

All employees taking part in *Activate Your Health* are asked to fill out an online self-administered questionnaire that is based on an adaptation of existing questionnaires, lifestyle guidelines and opinion of health experts. Participants are asked to provide basic socio-demographic, anthropometric, health, medication and work information and extreme values are checked before inclusion. Lifestyle habits are also auto-reported: PA (frequency, duration and intensity), eating habits, smoking, alcohol consumption, sleeping habits, and stress level. As the *Activate Your Health* program aims to modify the employees’ lifestyle habits, their intention to improve their habits is also evaluated. Once the questionnaire is submitted to Capsana, each of them is assigned a questionnaire ID to anonymize the data. The data are kept for 7 years by the Data Monitoring Committee. The Data Monitoring Committee is led by the principal investigator ([name]) in collaboration with one member of Capsana. It supervises data collection and analyses. For any further details please contact the principal investigator. After which, a total health score is calculated on 100 points: the higher the score, the better their health (100 equals optimal health and lifestyle habits). This score and action plan are sent to the employees personally.

### Detailed description of each intervention

#### Personalized online menus – year 1, 2, and 3

Each employee has access to an online platform called *SOScuisine*: it offers weekly menus, discounts, recipes and grocery shopping lists adapted to the employee’s preferences and health goals (improve cholesterol, manage diabetes, weight control, etc.).

#### Support in creating a favorable environment – year 1, 2, and 3

Health professionals visit each participating companies to host and present an information booth on how to create a favorable environment to improve their employees’ health (PA, nutrition and life balance). For example, they show the employees how to be active around their workplace, and highlight the healthiest menus in their cafeteria or vending machine in order to improve their eating habits.

#### Health challenge – year 1, 2, and 3

Employees are invited to participate individually or as a team in a 4-week activity called *Health Challenge*. It is publicized at their workplace and participation is voluntary. This intervention aims to guide companies and their workers towards better eating habits (i.e., five servings of fruits and vegetables/day), PA level (be physically active 30 min/day) and mental wellness (take time to relax). Capsana guides and motivates the employees who take part in this challenge. Employees who successfully fulfill the challenge receive an incentive (i.e., a sport bag). The participating company managed this intervention.

#### Conferences –year 1, 2, and 3

Different health professionals (nurse, kinesiologist, physician, psychologist, etc.) present a 60-min conference each at the work site of participating company at different time points into the study. The purpose of these sessions is to inform and educate employees on the importance of adopting and maintaining a healthy lifestyle. The health professional also gives tips and ideas to help employees achieve these goals. More conferences emphasizing mental well-being are planned.

#### Coaching – year 1, 2, and 3

Employees are offered assistance in maintaining or improving their lifestyle habits. They have the opportunity to talk, through the phone or in person, to a nurse and receive personal motivational coaching to enhance, among others, psychological health, well-being and lifestyle habits, and to reduce stress (Year 1). The following years, they will have the opportunity to talk to a nutritionist (Year 2), and to an exercise specialist/kinesiologist (Year 3).

#### Closing events – year 1, 2, and 3

At the end of each year, at the work site, employees will take part in a closing event organized by Capsana. An example of this is “Jeux Spin [31]” which consisted of various recreational activities such as soccer in an inflatable structure. It is to note that for logistic reasons, these events are offered to the participating companies (not just the participants of the *Activate Your Health* program). These events aim to congratulate the employees for taking control over their own health and motivate them to maintain their acquired/improved habits.

#### Health screening and flexibility assessment – year 1, 2, and 3

A team of nurses meets the employees individually to screen for their risk factors. The goal of this intervention is to identify any abnormal blood profile (unfasten state). It serves as an indicator and does not replace a regular blood test. If any abnormal results were found, employees were encouraged to consult their family doctor in order to do a follow-up. The plasma HDL level and HDL/total cholesterol ratio (CardioChek P.A.®-LIT001539, QC, Canada) and glucose concentration (Contour®Next - 85,303,759, New Jersey, US) are measured. Blood pressure is manually taken using the conventional auscultatory method (stethoscope: 3 M™ Littmann® Classic II S.E-MMM2201, US; sphygmomanometer: Welch Allyn & Tycos model, Boston, US). Employees are asked to stand erect in order to take their height using a vertical stadiometer (Seca213, Hamburg, Germany), and weighed using a scale (Tanita-BF-350, IL, US). Waist circumference is measured at the iliac crests using a measuring tape. The “sit-and-reach” test (Sit and Reach Test Tester- EN-121085, NY, US) is performed to determine posterior chain flexibility. The results of these tests are available to the employees at the end of their session, and the nurse gave appropriate health advice to improve their health profile.

#### CANRISK questionnaire – year 1, 2, and 3

During the screening session, participants also complete the CANRISK [32] questionnaire to determine their risk of developing prediabetes or diabetes. It consists of 12 multiple-choice questions, resulting in a score that is associated with three risk categories: low (< 21 points), moderate (21–32 points), and high (> 32 points). Employees also receive this score with the interpretation.

#### Distribution of publications – year 1, 2, and 3

During the conferences, screening and informational sessions, interested employees receive Capsana’s documentation (flyers/brochures/booklets/etc.) on chronic diseases (diabetes and cardiovascular health), mental health, medication, etc. These resources are also available on Capsana’s website.

#### Social health platform – year 1, 2, and 3

Each employee has access to a Social health platform (Sprout [33]), which allows employees to interact with one another. They can set goals, create an interest group, and challenge their colleagues and themselves. For example, an employee could challenge a colleague to take the stairs as often as they can.

#### Activity tracking – year 1

Capsana offered an accelerometer bracelet (Vívosport, Garmin, 2017) to 250 employees selected at random and invited them to track their own physical activity information through the Garmin website or phone application.

#### Optional: Quit to Win! Challenge

This intervention is part of the provincial program (« J’arrête, j’y gagne! ») initiated by Capsana [34]. Only the interested companies take part in this challenge. It is promoted at the workplace and information booth with documentation available to all the employees. Those who are interested are invited to stop their tobacco use for 6 weeks, and Capsana guides and assists the employees throughout. Employees are guided through this challenge and the winner receives an incentive such as a trip to Jamaica.

### Outcomes measures

Yearly assessments of a broad range of physical and psychological health outcomes will be performed to assess yearly changes and changes from baseline of each option.

#### Primary outcomes

Physical activity parameters, eating habits, smoking habits, alcohol consumption, sleeping habits, stress level and intention to improve these habits are measured.

#### Secondary outcomes

Waist circumference, weight, height, body mass index (BMI), plasma HDL and HDL/total cholesterol ratio, blood glucose concentration, systolic and diastolic blood pressure, flexibility level and risk factor profile are assessed.

### Statistical analyses

In future analyses, option D will be excluded as no company selected this option. To examine if the different options have similar baseline characteristics, i.e., to verify the homogeneity between the four options for the selected baseline variables one-way ANOVA analysis with the effect size (partial eta squared) and Chi-square test with Cramer’s V effect size will be used. Future studies will also explore the effect of each option on all outcomes. For continuous variables, mixed models for repeated measures with two factors will be used to analyze the effect of time and option on each outcome following one and 2 years of measurements. As for the categorical variables, generalized estimating equations (GEE) will be used. Possible confounders will be considered. Future studies will also take into account the cluster effect as the participants within the same company undergo the same implementation process and working environment, and therefore individual results from a same participating company could be dependent on each other. In future studies, intent-to-treat analysis will be used as well as multiple imputations. In addition, a particular consideration will be given to the sex and weight category of the participants.

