### Recruitment of participants/study population

Through phone calls and in-person meetings, Capsana contacted the different companies to participate in their *Activate Your Health* program. Eleven companies are taking part in the current project. Among the participating companies, six were related to banks, two were related to financial markets, one was a graveyard parish, one was related to workplace health safety and security, and one was a marketing firm. The participating companies encouraged their employees to take part in this WHPP and participation was on a voluntary basis. Only pregnant women could not partake in the program. After an information session about the *Activate Your Health* WHPP and motivating their willingness to participate, an email was sent out to all the employees. Those who completed the online consent form (written) were able to fill the self-administered questionnaire.

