### Study intervention/allocation to interventions

Capsana and their sponsors are offering the interventions throughout the year and at the same time of year throughout the 3-year period (ex: a company that received an intervention in January 2017 will receive the same intervention in January 2018, 2019). Table 1 summarizes the different interventions included in each of the five options (A to E) and the number of companies enrolled in each of them. Briefly, option A had the most extended number of interventions, and involved numerous web-based and innovative tools to improve lifestyle habits. Moreover, some interventions in option A and B were tailored and personalized to the participants’ needs while participants in option E will not receive any interventions other than the informational/motivational sessions at baseline and at the end of each year (control group). There was no concomitant care or interventions that were prohibited while taking part in this program.

**Table 1 Tab1:** Details on the interventions included in each option (*n* = 11 companies)

Interventions	Options				
	Extensive				Limited
	A (*n* = 1)	B (*n* = 1)	C (*n* = 8)	D (*n* = 0)	E (Control) (*n* = 2)
Personalised online menus	X	X	X	X	
Support in creating a favourable environment	X	X	X	X	
*Health Challenge*	X	X	X	X	
Conferences	X	X	X		
Coaching	X	X	X		
Closing events	X	X	X		
Health screening and flexibility assessment	X	X			
CANRISK questionnaire	X	X			
Distribution of publications	X	X			
Social health platform	X	X			
Activity tracker	X				
*Optional: Quit to Win! Challenge*	X	X			

The companies had to choose one out of the five options offered by Capsana. Most of the companies (*n* = 8) chose option C and none picked option D. One company chose two different options (one group was placed in option A while the others in option E). One company won a promotional draw and Capsana placed it in one of the five options (Option E). In-person interventions took place at the workplace whereas the web-based ones were accessible anywhere.

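### The baseline homogeneity tests ignore company, so their p-values are not valid evidence about the options, and a non-significant result cannot establish balance

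*Protocol article*

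**What the plan says.** All references are to the protocol article.

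- **Statistical analyses** names the baseline tests and their purpose: "to verify the homogeneity between the four options for the selected baseline variables one-way ANOVA analysis with the effect size (partial eta squared"), and for categorical variables "Chi-square test with Cramer’s V effect size will be used". Neither test is given a company term, and no significance level is stated.
- The same section later says "Future studies will also take into account the cluster effect as the participants within the same company undergo the same implementation process and working environment", giving as the reason that "individual results from a same participating company could be dependent on each other". This comes after the mixed models and generalized estimating equations for the outcomes and is not tied to the baseline comparison.
- **Recruitment of participants/study population**: "Eleven companies are taking part in the current project".
- **Study intervention/allocation to interventions** makes the company the chooser: "The companies had to choose one out of the five options offered by Capsana". The resulting spread was uneven: "Most of the companies (*n* = 8) chose option C and none picked option D". Table 1 adds one company in A, one in B and two in E. "One company chose two different options (one group was placed in option A while the others in option E"). That split explains why the option counts sum to 12 for 11 companies.

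**The concern.** One-way ANOVA and chi-square, as named, take the employee as the independent unit. The option was set by company, with one exception where groups within a company were separated. Under the article's own premise of dependence within companies, an option mean carries company variation that these tests leave out of the error term. The p-value then reflects differences among a few particular companies as much as differences among options.

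Two further problems do not depend on the size of the correlation. First, failing to reject does not show that groups are alike, so such a test cannot verify homogeneity. Second, A and B rest on one company each. For B, option and company are the same thing. For A, the only contrast that holds company constant is with the E part of the split company, and there option coincides with the group that was placed in it. No test can separate these.

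At stake is how readers judge the comparability of self-selected groups.

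**Working it through.** The article gives no level, ICC or error rate for these tests, so there is no stated figure to reproduce. The check asks how often the planned tests reject when options do not differ beyond company variation.

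**Inputs from the article**
- 11 companies forming 12 option-by-company cells: A 1, B 1, C 8, E 2, one company shared by A and E.
- N = 6000, the potential enrolment under Intended sample size explained. N = 656, the pilot size in the same section, serves only as a low bound. 1500 and 3000 are intermediate values.

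**Assumptions**
- Level 0.05; ICC 0.005 to 0.05.
- Company sizes either equal, or unequal with relative sizes 3 for the split company (half in A, half in E), 0.5 for B, 2.5 down to 0.2 across the eight C companies, and 0.5 for the other E company.
- Binary variables have prevalence 0.20.

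**Design effect**

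1 + (m − 1) × ICC, with m = N/11.
- N = 6000, m = 545.5: 1 + 544.5 × 0.005 = 3.7; 1 + 544.5 × 0.01 = 6.4; at ICC 0.05, 28.2.
- N = 656, m = 59.6: 1 + 58.6 × 0.005 = 1.3; 1 + 58.6 × 0.01 = 1.6; at ICC 0.05, 3.9.

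**Simulation**

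Company is a random effect with variance equal to the ICC (total variance 1) and there is no option effect. Each scenario has 4000 replicates. The individual-level ANOVA uses F with 3 and N − 4 df; the chi-square has 3 df.

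ANOVA rejection rate in % (equal / unequal company sizes):

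| N | ICC 0.005 | ICC 0.01 | ICC 0.02 | ICC 0.05 |
|---|---|---|---|---|
| 656 | 9 / 10 | 15 / 15 | 26 / 27 | 50 / 49 |
| 1500 | 16 / 19 | 27 / 30 | 47 / 46 | 73 / 70 |
| 3000 | 27 / 30 | 47 / 47 | 68 / 64 | 88 / 82 |
| 6000 | 46 / 48 | 66 / 65 | 83 / 79 | 94 / 91 |

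Chi-square rates lie within about 3 points of these and reach 95% at N = 6000 and ICC 0.05. At ICC 0 both tests reject 4 to 5%, as they should.

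**Effect sizes in the same runs**

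At N = 6000 the median partial eta squared is 0.001 to 0.008 over ICC 0.005 to 0.05. Many of the significant results would be small.

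**A company-level alternative**

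ANOVA on the 12 cell means has 3 and 12 − 4 = 8 df. Over ICC 0.005 to 0.05 it rejects about 4 to 6% at N = 6000 and 3 to 8% across all N. Eight residual df mean very low power. This version also treats the two halves of the split company as separate units.

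**The case against.** **Allocation was not randomised.** A company difference that lines up with option is a genuine imbalance between the groups being compared, and flagging it is no mistake. This stands. A reader might infer that significant baseline differences are spurious and mislead about comparability; the design does not support that. What fails is the p-value as evidence about options rather than about these particular companies.

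**Effect sizes are already planned.** Partial eta squared and Cramer's V will show that many significant results are small. This stands in part: they temper over-reading, but they do not separate company from option either.

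**The cluster sentence may be meant to cover everything.** It does not name the outcome models, and the article is condensed. But it follows those models, nothing links it to the baseline tests, and the tests named cannot carry a company term. If it was meant to cover baseline, the named tests still have to change.

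**Some consequences would be inference.** A reader might conclude that company differences will be declared option differences in a large share of tests. The article states no level and no rule for declaring imbalance, and the share depends on unstated ICC and company sizes. A reader might also suppose that these tests will select the confounders, or that they are the first analysis due. The article says only that possible confounders will be considered and sets no order of analyses.

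**Conclusion.** The point holds in a limited form. The article specifies tests that conflict with its own statement about dependence within companies, and it gives them a purpose, verifying homogeneity, that no non-significant test can serve.

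The inflation depends on assumptions. At a 5% level and ICC 0.005 to 0.01 it is modest at N = 656 (about 9 to 15%) and severe at N = 6000 (about 46 to 66%). It rises to about 95% at N = 6000 with ICC 0.05. The null behind these figures treats companies as random draws with no option effect.

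That A and B each rest on a single company, and that non-significance does not show balance, hold whatever the ICC. The outcome models are separate from these tests and are not directly affected, so this is a fault in the baseline comparison and not in the effectiveness analysis.

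**What to change.** Under Statistical analyses, remove the homogeneity p-values and the claim to verify homogeneity. Present baseline characteristics descriptively, by option and by company, with standardised differences between options. State beside the table that A and B rest on one company each and that A shares its company with part of E.

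If a test is kept, make it account for company, through company-level means or a random company effect. State its very low power (about 8 residual df), so that non-significance is not read as balance.

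The descriptive version costs a change of wording and a different table, with no new data. Keeping a company-level test has a real drawback: it could easily miss an imbalance that matters for confounding. That favours description over testing.

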**Methods/design:**

Eleven companies are taking part in this WHPP and had to choose among five different options of this program and all their employees were encouraged to participate. Each option differs by the number and type of interventions included. The limited option, which is considered the control group, only consists in completing a questionnaire regarding their health status, lifestyle habits and behaviors. On the other end, the extensive option receives a combination of multiple interventions: online menus, health challenges, support in creating a healthy work environment, coaching by health professionals (nurse, nutritionist, and kinesiologist), health screening and flexibility assessment, online resources, social health platform, and activity tracking. The remaining options are in between these options and vary by the amount of intervention. Baseline data are already gathered; two other data collection periods will take place after one and 2 years into the program. The primary outcomes of the current program are physical activity and fitness measures, nutritional data, smoking habits, stress and intention to change.

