One of the advantages of the *Activate Your Health* program is the varying number of interventions, which allows us to compare the effect of different combinations of interventions on health and work-related variables. We did exclude the option D as none of the companies chose that option. We can deduct that such an option might be less appealing for companies. It would have been interesting to compare the option A, which contains all the interventions targeting eating and PA habits vs. the option D, which had only interventions improving eating habits. Nevertheless, we do have the limited option (control group) that did not receive any interventions to compare the effectiveness with the other options. Moreover, Nöhammer et al. (2010) suggested that WHPP could benefit from documenting the employee’s perspective of the interventions. At the end of the current WHPP, a questionnaire regarding each intervention will be sent to all the employees, in order to study their perspective. Also, throughout the year, Capsana also supports each company in the creation of a favorable environment by providing advice and/or help [46]. Modifying the work environment by decreasing unhealthy food available at the work site within the company, for example, could have positive impact on the employees’ health and the organization as a whole [46].

Some limitations should be considered. The data collection method consists of filling questionnaires. Most of the variables of interest, such as PA level and eating habits, in the current program and its variations come from these self-reported answers. Objective measures such as accelerometer data could have been used to identify the changes that are taking place within the different options. Moreover, participants who have successfully changed their lifestyle habits will be more inclined to remain actively involved in the *Activate Your Health* program, and to be reassessed, which was the case in another study [47]. In addition, Nilsen et al. [47] (2014) noted the majority of their participants with diabetes who dropped out were the participants with a poor life satisfaction and needed help with their lifestyle habits. Taking these observations into account, specific analysis will be performed to examine this aspect in *Activate Your Health*.

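### The screening outcomes (HDL, cholesterol ratio, glucose, blood pressure, flexibility) are described only for options A and B, so their planned effects cannot be estimated for option C or control E

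*Protocol article*

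**What the plan says.** **Outcomes.** The Secondary outcomes section lists waist, weight, height and BMI, and then: "plasma HDL and HDL/total cholesterol ratio, blood glucose concentration, systolic and diastolic blood pressure, flexibility level and risk factor profile are assessed". It does not restrict any of them to particular options. The opening of Outcomes measures plans yearly change, and change from baseline, for each option.

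**Analysis.** The Statistical analyses section drops option D, which no company chose, and keeps four options. It then states: "Future studies will also explore the effect of each option on all outcomes". The method it names for outcomes on a continuous scale, with follow-up at one and two years, is this: "mixed models for repeated measures with two factors will be used to analyze the effect of time and option on each outcome". On missing data the section says only that "intent-to-treat analysis will be used as well as multiple imputations".

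**Data source.** Lipids, glucose, auscultatory blood pressure, tape-measured waist and the sit-and-reach test are described in one place only, the screening entry under Detailed description of each intervention. The Table 1 row reads "Health screening and flexibility assessment X X": two marks, under A and B, with C, D and E blank.

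**Control.** According to the abstract, option E "only consists in completing a questionnaire regarding their health status, lifestyle habits and behaviors". The Discussion nevertheless says: "we do have the limited option (control group) that did not receive any interventions to compare the effectiveness with the other options".

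**The concern.** Here the measurement is itself one of the interventions, so an option without the screening is also an option without the data. The article lists the screening measures as outcomes for every option and names E as the comparator, but describes no measurement visit in C or E.

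What is at stake is the study's only set of objective health measures. The Discussion counts healthy blood pressure, cholesterol and glycaemia among the targets that make the programme strong. It also sets the programme against an earlier study that it notes had no control group. On the screening measures this study has no control group either, and the limitations paragraph does not say so. A reader could take a change in blood pressure or lipids in A or B for a controlled programme effect. Ageing, regression to the mean and the advice to see a family doctor after an abnormal result could each produce such a change.

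**Working it through.** The plan states no sample size, power or effect size for these outcomes, so there is no figure to reproduce. The check is whether the planned contrasts can be estimated from the data described.

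**Step 1: source of each outcome**

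| Outcome | Described source | Options with that source |
|---|---|---|
| HDL, HDL/total cholesterol ratio, glucose | nurse screening | A, B |
| Systolic and diastolic blood pressure | nurse screening | A, B |
| Flexibility (sit-and-reach) | nurse screening | A, B |
| Waist | nurse screening; possibly a questionnaire item | A, B; others uncertain |
| Weight, height, BMI | nurse screening; plausibly self-reported anthropometrics | A, B measured; all options plausibly self-reported |

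The first three rows hold six measures with no described source outside the screening. Weight, height and BMI are outside this point. The risk factor profile is undefined. If it uses screening results or CANRISK, which Table 1 also marks for A and B only, it belongs with the six.

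**Step 2: count of placements and companies** (Table 1 and the text below it)

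- Placements: A 1 + B 1 + C 8 + E 2 = 12.
- Companies: 12 − 1 = 11, because one company is split between A and E.
- Placements with screening: 1 + 1 = 2. Without: 12 − 2 = 10.
- Companies with any screening values: the split company, through its A group, and the B company, so 2. Without: 11 − 2 = 9.

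**Step 3: estimability**

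Take the two-factor model as option (A, B, C, E) by time (baseline, year 1, year 2), with interaction.

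- Fixed-effect parameters: 4 × 3 = 12.
- Parameters identified when only A and B have data: 2 × 3 = 6. A rank check of the design matrix gives the same: rank 6 of 12.
- The contrast in change to year 2 between options *i* and *j* is (μ_i2 − μ_i0) − (μ_j2 − μ_j0). It can be estimated only if both options have data.

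| Contrast | Estimable? |
|---|---|
| A vs B | yes |
| A vs C | no |
| A vs E | no |
| B vs C | no |
| B vs E | no |
| C vs E | no |

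Without the interaction, the terms for C and E would still meet no data.

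**Step 4: what A versus B can show**

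A is one group within one company and B is one other company. With one company per option, an option difference and a company difference are the same quantity. The planned allowance for clustering cannot separate them. In Table 1 the activity tracker is the only item that A has and B lacks.

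**The case against.** The strongest defence is one of scale. The study is quasi-experimental and exploratory, the paper's stated aim is to describe the programme, and the affected measures are secondary. Everything in the Primary outcomes section is covered by the questionnaire that all options complete. The Discussion already concedes reliance on self-report, and its sentence about the control group does not mention biometric measures. All of this stands, and it limits how serious the point is. It does not remove it: an exploratory label does not make a contrast without data estimable. Nor could an unseen analysis plan recover the values. Baseline collection ended in July 2018, so screening C or E later could not give change from baseline.

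Four stronger readings are tempting, and the documents do not support them.

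- **That values for C and E will be imputed.** The article mentions multiple imputation without giving its scope. The ordinary reading is dropout, which the Discussion takes up. Nothing says it will fill in measures never scheduled in an option. If it did, the results there would rest wholly on the imputation model's assumption about the option effect, so the scope is worth stating.
- **That waist is certainly absent in C and E.** The questionnaire collects anthropometric information without listing the items, so a self-reported waist cannot be excluded.
- **That the baseline comparison of the four options includes these measures.** That check covers selected variables, and the selection is not given.
- **That a primary outcome is affected.** The abstract counts fitness measures as primary, but the Primary outcomes section does not list them, and flexibility appears under Secondary outcomes.

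**Conclusion.** The point holds for six secondary measures: HDL, HDL/total cholesterol ratio, glucose, systolic and diastolic blood pressure, and flexibility. It holds for waist too if the questionnaire does not collect it. The article plans effects of each option on outcomes that, by its own Table 1, are collected in 2 of 12 placements and 2 of 11 companies. Five of the six pairwise option contrasts, including every contrast with control, cannot be estimated. The sixth, A versus B, is fully confounded with company.

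This rests on two readings: that the two marks in the screening row belong to A and B, as the layout of the table indicates, and that no screening outside the described intervention took place in C or E. It needs no assumed standard deviation, effect size or sample size.

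The contradiction lies within the article and should be corrected. Because the measures are secondary and the study exploratory, it does not undermine the study as a whole.

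**What to change.** 1. In Outcomes measures and Secondary outcomes, state that the screening outcomes are available in options A and B only. Say whether waist is also collected by questionnaire, and what the risk factor profile is built from. If C and E were in fact measured, say how and when.
2. In Statistical analyses, report these outcomes as uncontrolled change within A and within B. Label any A-versus-B contrast exploratory and company-confounded. Exclude C and E from these models and, if any of these measures were selected for it, from the baseline check.
3. State that multiple imputation applies only where the outcome was scheduled to be measured in that option.
4. In the Discussion, limit the comparison with control to outcomes collected by questionnaire in all options, and list the missing control data for the screening outcomes as a limitation.

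The cost is a few sentences and no new data collection. The downside is that the sponsor gives up controlled claims on the biometric outcomes, which the design as described cannot support.
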